### Who will take informed consent? {26a}

The informed consent will be taken by the clinical supervisors of the study.

If patients are conscious and capable of giving consent, they will be informed in detail about the study aims, procedures, risks, and benefits, and written informed consent will be obtained directly.

In cases where the patient is temporarily incapable of giving informed consent due to sedation or medical condition, legal representatives (court-appointed guardians or next of kin) will be contacted to obtain proxy consent.

Specifically, in accordance with current German legislation, the so-called “Ehegattennotvertretungsrecht” (spousal emergency representation) is applied if applicable. This allows the patient’s spouse to provide proxy consent in emergency situations, as confirmed by the local ethics committee.

Once patients regain full decision-making capacity, they will be re-informed, and consent will be reaffirmed or withdrawn as appropriate.

### Additional consent provisions for collection and use of participant data and biological specimens {26b}

No additional use of the data or biological samples beyond the scope of this study is planned. Accordingly, no specific consent for ancillary studies is required or obtained.

## Interventions

### Explanation for the choice of comparators {6b}

#### Sham-Control Group (Sham-BFR)

The control group is receiving the standard intensive care which also includes a daily physiotherapy session. To reduce the intervention bias, a daily"Sham"BFR intervention is also provided. The"Sham-BFR"intervention is performed in an intermittent manner on both thighs, according to the protocol of intervention group 1 (see below), but with the minimum standard pressure of 20 mmHg. This group serves to demonstrate the"clinically standard"progression of our test subject population and the changes are used as a basis for comparison with our intervention groups.

### Intervention description {11a}

#### Experimental intervention group 1: blood flow restriction/ischemic preconditioning (BFR/IPC) training

The first intervention group receives a daily BFR/IPC intervention of the lower extremities with 100% of the individual limb occlusion pressure (LOP). BFR training involves the application of tourniquets during a passive or active exercise intervention in order to provide an additive metabolic stimulus. The tourniquets are applied as proximal as possible to the thigh and a pressure is applied that temporarily occlude venous return with associated reductions/ complete blocking of arterial inflow [27]. For BFR/IPC training, a CE-certified surgical-grade tourniquet autoregulation device (CE-9–2200-001BFR-C, Delfi Medical Innovations Inc., Vancouver, Canada) is used. The applied exercise pressure is calculated by the individual limb occlusion pressure (LOP) using the BFR/IPC device at the start of each training session. The patient lies in bed at rest while the cuff is inflated until no more blood flow can be detected in the limb (= LOP). From this occlusion pressure, 100% is subsequently applied for the BFR/IPC intervention. The intervention protocol consists of daily exercise sessions of 50 min at intervals, whereby both thighs are exercised alternately (5 min occlusion + 5 min free flow, 5 times in total) over a period of 7 days [28].

#### Experimental intervention group 2: electromyostimulation (EStim)

The second intervention group receives a daily Sham-BFR/IPC intervention of 20 mmHg combined with electrical muscle stimulation training (EStim). For EStim, two self-adhesive electrodes (Axion Medical, Axion GMBH, Villengen-Schwennigen, Germany) are applied to the vastus lateralis muscle and two electrodes to the vastus medialis muscle. The stimulation parameters are as follows: frequency 50 Hz, work cycle 10 s stimulation followed by a 10-s pause and pulse width 400 µ. The EStim protocol is only applied during the occlusion phases of the Sham-BFR/IPC protocol. The intervention protocol consists of daily exercise sessions of 50 min at intervals, whereby both thighs are exercised alternately (5 min occlusion + 5 min free flow, 5 times in total) with the “Sham-BFR/IPC” pressure of 20 mmHg and the additional EStim Protocol over a period of 7 days. There is a coupling between the BFR and the EStim device (Mi-Theta 600; Cefar Compex), which only enables EStim during the phases of occlusion. If the limb is reperfused by releasing the air from the cuff, the EStim signal is interrupted and only reactivated when occlusion resumes.

#### Experimental intervention group 3: BFR/IPC-Training + EStim

The third intervention group combines BFR/IPC training with 100% of the individual limb occlusion pressure with EStim training. Within this intervention group both previously described interventions will be combined. For BFR/IPC training, 100% of the individual LOP is applied, whereas the EStim parameters are as follows: frequency 50 Hz, work cycle 10 s stimulation followed by a 10-s pause and pulse width 400 µ. The intervention protocol consists of daily exercise sessions of 50 min at intervals, whereby both thighs are exercised alternately (5 min occlusion + 5 min free flow, 5 times in total) over a period of 7 days. There is a coupling between the BFR/IPC and the EStim device (Mi-Theta 600; Cefar Compex), which only enables EStim during the phases of occlusion. If the limb is reperfused by releasing the air from the cuff, the EStim signal is interrupted and only reactivated when occlusion resumes.

### Criteria for discontinuing or modifying allocated interventions {11b}

Drop-out of a patient from the study: One or more of the following circumstances may lead to a patient discontinuing the study (these patients are counted as drop-outs): Withdrawal of consent by the patients or their legal representatives without giving reasons; Occurrence of an exclusion criterion; Violation of the study protocol.

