**Methods:**

This prospective, randomized controlled trial will recruit 120 patients from the surgical ICU at the University Hospital Bonn, who meet the inclusion criteria of a > 48-h ICU stay. Patients will be randomized into four groups: Sham-Control, BFR/IPC, EStim, and combined BFR/IPC + EStim. The study’s primary endpoints include feasibility and safety metrics, such as patient compliance and stress response, alongside secondary endpoints related to clinical outcomes like ICU length of stay, ICUAW prevalence, muscle mass preservation, and rehabilitation efficacy. Measurements include non-invasive assessments of muscle mass, intramuscular microdialysis to monitor metabolic and inflammatory markers, and health-related quality of life evaluations post-discharge.

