#### Clinical feasibility, safety and acute muscle condition

To assess the clinical feasibility and safety of the applied interventions and diagnostic techniques on patients’ mental and physical health, the following endpoints are investigated in this study:*Feasibility*: Questionnaires regarding patient compliance (e.g., acute measure of recovery and stress, AEB) and possible stress response to the interventions (e.g., VAS 0–100 mm).*Global Health & Safety*: Changes in drug application for supporting the cardiovascular system (e.g., noradrenaline), use of analgetic (e.g., fentanyl) and sedation drugs (e.g., propofol) and changes in respiratory gases before, during and after each intervention session. Daily assessment of inflammation and coagulation parameters.

Since ICUAW and the resulting complications in the process of rehabilitation can be attributed to compromised muscle health, specific outcome parameters were selected that allow an objective description of possible positive or negative effects of the course of therapy, applied interventions, and further hospitalization on skeletal muscle conditions. These parameters will be partially recorded daily or before and after the intervention period, as well as by discharge from the ICU and hospital:*Muscle Health*: Muscle mass and fiber angle, muscle strength, neuromuscular activation, body composition (by bioelectrical impedance analysis).

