### Eligibility criteria {10}

Patients will be recruited on the ICU of the University Hospital Bonn. The patient inclusion criteria are as follows: (1) The study includes all patients under intensive care monitoring and therapy with a length of stay > 48 h in the surgical intensive care units of the University Hospital Bonn. (2) All participating patients have signed the patient consent form for study participation as well as the privacy policy after comprehensive explanation, explanation and information or have been represented by the spouse as part of the spouse’s emergency representation after comprehensive explanation. (3) Patients aged > 18 years are included. Exclusion criteria for the study are: (1) acute or chronic infections of the extremities, (2) open wounds on the lower extremity, (3) Pregnancy and breastfeeding, (4) sickle cell anemia, and (5) former surgical interventions on the thigh vessels (e.g., stenting, bypassing).

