#### Drop outs and rate of loss to follow-up

Data from patients who withdraw their consent to participate during the intervention period of the study will remain in the analysis. If the patients consent to participate in the follow-ups, they will be analyzed as “intent-to-treat” within their original treatment group allocated by randomization.

Based on our experiences with the SepsisDataNet.NRW cohort (a large multicenter study on sepsis patients), we expect a loss to follow-up (30-day survival) of about 10%. Based on our experience from the health-related quality of life study in ECMO patients (see unpublished data above), we expect a follow-up rate of 75% from patients still alive at the time-point of 6-month follow-up. Due to the expected heterogeneity of the study population, no estimation of mortality in the study group can be done at this point.

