## Statistical methods

### Statistical methods for primary and secondary outcomes {20a}

#### Data acquisition

All patients will undergo the standardized study protocol. Per each day, measurements will be repeated thrice per time point. The median of these technical replicates will be used as the repeated measurement value for said time point. For descriptive purposes values will be reported as median ± interquartile range or absolute number and percent, where appropriate.

Primary analysis method will be an ANCOVA with Dunnett’s test with the measurement after 7 days as outcome and adjusted for the baseline value. Additionally, mixed models will be fitted to assess the sensitivity of the results under consideration of all measurement points. Health-related quality of life will be analyzed using mixed models for repeated measurements. Again, joint models may be considered to take a considerable proportion of missing data into account. Time-to-event outcomes, such as length of ICU stay, length of hospital stay, and time to return to work, will be analyzed using Kaplan–Meier estimates and Cox regression models.

All primary, secondary, and other exploratory outcomes will also be reported descriptively. Patients who decide to drop out of the study prior to completion of the intervention will remain in the study analysis and their respective study cohort following an intention-to-treat analysis. Recruitment will commence until the overall number of 120.

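### The drop-out rule in {11b} merges stopping the intervention with leaving the study, so day-7 and later outcomes can be lost for treatment-related reasons, and the intention-to-treat wording does not name these drop-outs

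*Protocol article*

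**What the plan says.** Section {11b} is headed as criteria for stopping or changing the allocated intervention, but it contains only reasons for leaving the study. The listed circumstances "may lead to a patient discontinuing the study (these patients are counted as drop-outs"). Besides withdrawal of consent they are "Occurrence of an exclusion criterion; Violation of the study protocol". The same text stands again in the allocation part, after {16a}. Nowhere does the article describe a patient who stops the intervention and continues to be assessed.

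The exclusion criteria in {10} begin "1) acute or chronic infections of the extremities, (2) open wounds on the lower extremity", and both can arise during the treatment week.

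Three places deal with patients who leave:
- {20a}: "Patients who decide to drop out of the study prior to completion of the intervention will remain in the study analysis", in their own cohort, under intention-to-treat.
- The drop-out paragraph under {11c}, repeated in {20c}: "Data from patients who withdraw their consent to participate during the intervention period of the study will remain in the analysis". It continues "If the patients consent to participate in the follow-ups, they will be analyzed as" intention-to-treat in the randomised group.
- {20c}: multiple imputation if data are missing at random. If violations or discontinuation leave a considerable amount of data missing, joint models are to be considered.

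**The concern.** Two of the three triggers are post-randomisation events that the intervention can influence. A leg wound or limb infection can follow from a thigh cuff, electrodes or the intramuscular catheter. The catheter is planned for every arm, but full occlusion and stimulation are not, so the frequency of such events can differ between arms. Violation of the protocol is not defined in the article and may also depend on how well an arm's procedure is tolerated.

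If such a patient leaves the study, the day-7 measurement on which the primary ANCOVA rests is not taken, nor are the later study assessments. The daily laboratory series and the per-session drug and vital-sign records also stop at the point of possible harm. The comparison with sham is then made among patients selected by something that happened after randomisation. The article does not say who decides or by what criterion, and under {17b} clinical staff are not blinded.

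**Working it through.** **1. Which drop-outs are covered**

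| Reason for leaving under {11b} | Who triggers it | Named in a retention sentence? |
|---|---|---|
| Withdrawal of consent | patient or representative | yes: {11c}, {20a}, {20c} |
| New exclusion criterion | study team | no |
| Protocol violation | study team | not in the intention-to-treat sentences; {20c} mentions it only as a source of missing data |

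The last two groups are not declared excluded. They are simply not named. {20c} itself expects violations and discontinuation to leave data missing.

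**2. Whether the analysis can repair the loss**

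Imputation under missing at random needs patients with the event whose day-7 value is known. If the rule is applied to everyone with the event, there are none, and post-event values are filled in from patients without it. Joint models replace this with an assumption about the link between leaving and outcome, which the trial's own data could not check. Continued measurement avoids the problem.

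**3. The plan's own power figure**

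Inputs from {14}: effect 2.8 − 2.1 = 0.7 mm; follow-up SD 2 mm; correlation 0.9 (the article says above 0.9); 30 per arm; Dunnett's test for three comparisons with control. Assumed, because the article states no level: two-sided 5% family-wise.

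- Residual SD = 2 × √(1 − 0.9²) = 0.872 mm
- Standard error = 0.872 × √(1/30 + 1/30) = 0.225 mm
- Non-centrality = 0.7 / 0.225 = 3.11
- Dunnett critical value (115 df) = 2.38
- Power = 76.6%, or 76.3% with a small allowance for estimating the baseline slope

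This agrees with the stated minimum of 75%, with all 30 patients per arm evaluable.

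**4. Effect of loss on power (loss assumed)**

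| Evaluable patients | Standard error (mm) | Non-centrality | Power |
|---|---|---|---|
| 30 in each arm | 0.225 | 3.11 | about 77% |
| 27 in each arm (10% loss) | 0.237 | 2.95 | about 71% |
| sham 29, each active arm 25 | 0.238 | 2.94 | about 71% |
| 25 in each arm | 0.247 | 2.84 | about 67% |

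At correlation 0.92 the first two rows become about 86% and 81%.

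**5. Effect of selective loss on the estimate (loss and difference assumed)**

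Suppose 5 of 30 active and 1 of 30 sham patients lose their day-7 value, and that those lost would have measured 0.7 mm (the design effect) below the rest of their arm. A complete-case difference is then shifted by (5/30 − 1/30) × 0.7 = 0.093 mm, which is 0.093 / 0.7 = 13% of the design effect, in favour of the active arm. The shift is proportional to both assumptions and vanishes if either difference is zero.

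**The case against.** A reader might infer that every violator is automatically removed, that drop-outs are left out of the analysis, and that harms therefore disappear from the active arms. The documents support none of this.

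- The rule is permissive: the events can lead to discontinuation but need not.
- No sentence excludes drop-outs or discards recorded data. {20a} states an intention-to-treat analysis, and data are kept even after consent is withdrawn. The consent condition in {11c} and {20c} concerns later follow-up, where consent is needed.
- A wound or infection has to occur before it can trigger drop-out. {22} requires adverse events to be documented, graded and followed until they resolve or stabilise, and events of Grade 2 or higher and serious events to be published.

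It is also tempting to say that missed sessions are the feasibility endpoint itself. The abstract says the "primary endpoints include feasibility and safety metrics, such as patient compliance and stress response", but the objectives measure feasibility by "Questionnaires regarding patient compliance (e.g., acute measure of recovery and stress, AEB") and a visual analogue scale. A violation is not an endpoint as the article defines it.

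Further, {20c} foresees joint models for this kind of missing data, some outcomes (length of stay, discharge status, costs) come from routine hospital data, and the trial design section disclaims power for definitive efficacy conclusions.

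All of this stands and limits the point to outcome collection after the event. It does not answer that point. Discretion without a stated criterion, where clinical staff know the allocation, is itself a route to selective loss. Remaining in the analysis set does not supply a measurement that was never taken, and the joint models are only to be considered. Who continues to be assessed is a rule of conduct that this article does state, so it cannot be left to an analysis plan.

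**Conclusion.** The point holds in this limited form. {11b} and its repetition join two decisions that should be separate. Applied as written, the rule can lose day-7 and later outcomes for reasons that treatment may cause, and the intention-to-treat sentences do not explicitly reach patients taken off for a violation or a new exclusion criterion. It does not show that recorded harms are removed or that any drop-out is excluded from the analysis.

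The size cannot be derived, because the article gives no frequency for either trigger. Under the assumed losses above, arm-specific power falls from about 77% to about 71%, and a complete-case estimate could shift by about 0.09 mm against a design effect of 0.7 mm. These figures rest on SD 2 mm, correlation 0.9, a two-sided 5% family-wise level and the assumed loss patterns. Selective loss matters more than the loss of power, because no later analysis can recover the missing measurements.

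**What to change.** - In {11b} and its repetition after {16a}, state that a protocol violation or an exclusion criterion arising after randomisation is recorded, with date and reason, and does not end study participation. Day-7, discharge and telephone assessments continue as scheduled. Only withdrawal of consent to data collection ends follow-up.
- In the drop-out paragraph under {11c}, in {20a} and in {20c}, state that all randomised patients are analysed in their allocated arm, whatever the reason for discontinuation.
- Leave open whether the intervention itself continues after such an event. That is a clinical decision outside this point.

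The cost is a change of wording and a few assessments in patients who are off the intervention, all of them already scheduled. The article gives the trial status as in preparation, so the change should be made before enrolment begins.

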### Strategies to improve adherence to interventions {11c}

#### Compliance to the intervention techniques

The compliance to the applied intervention techniques is assumed to be high based on experience from in-house studies in orthopedic patient populations. Passive BFR training was able to significantly reduce the subjective perception of pain and preserve muscle mass in the hospitalized phase after primary knee joint arthroplasty or spinal surgery (*unpublished data, data available for reviewers’ eyes only upon reasonable request*). Thereby, the technique was applied starting from the first day after surgery.

#### Drop outs and rate of loss to follow-up

Data from patients who withdraw their consent to participate during the intervention period of the study will remain in the analysis. If the patients consent to participate in the follow-ups, they will be analyzed as “intent-to-treat” within their original treatment group allocated by randomization.

Based on our experiences with the SepsisDataNet.NRW cohort (a large multicenter study on sepsis patients), we expect a loss to follow-up (30-day survival) of about 10%. Based on our experience from the health-related quality of life study in ECMO patients (see unpublished data above), we expect a follow-up rate of 75% from patients still alive at the time-point of 6-month follow-up. Due to the expected heterogeneity of the study population, no estimation of mortality in the study group can be done at this point.

### Relevant concomitant care permitted or prohibited during the trial {11 d}

#### Additional treatments

The present study will be carried out in addition to the routine treatment of the ICU to the existing guidelines of the S3 guideline of the German Society for Anesthesiology and Intensive Care Medicine e.V. (DGAI) “Lagerungstherapie und Mobilisation von kritisch Erkrankten auf Intensivstationen.” By participating in the study, patients do not receive any additional study-related procedures/medications except for the investigated study interventions. Furthermore, patients participating in this study will not be refused any intervention/medication if this is necessary in the course of their care.

### Provisions for post-trial care {30}

N/A

### Outcomes {12}

For this research project, examinations will be divided into basal-, continuous-, and in-exercise measurement batteries (Fig. 2).

**Fig. 2 Fig2:**
[figure not shown]
Study flow chart

Basal examinations

All participating patients will go through a series of measurements before and after the intervention period of seven continuous days, as well as after discharge of the ICU and discharge of the hospital.Muscle Analysis I (Non-invasive):Muscle mass of the thigh muscles, which represents a correlation to the full body muscle mass [29], and fiber angle will be obtained by ultrasound and analyzed through a software-based post-processing pipeline. To determine grip strength, which shows a positive correlation with total body strength [30], a measurement of both hands is carried out using a hand dynamometer (Dynamo, Vald, Brisbane, Australia). An isometric maximum strength test is performed on both lower extremities during the following exercises: Dorsiflexion of the foot, plantar flexion of the foot, hip flexion, and knee extension. During this process, surface electromyography (Picoblue, Cometa, Bareggio, Italy) is used to analyze neuromuscular activation of the M. rectus femoris and M. vastus lateralis during the exercise.Global Health:For analyzing the global health status of the participating patients, routine laboratory measurements, containing, e.g., inflammation parameters (e.g., C-reactive protein, leucocytes), electrolyte concentrations, parameters of kidney- and liver function, will be measured daily. Additionally, the application of drugs for supporting the cardiovascular system (e.g., noradrenaline), analgesics (e.g., fentanyl), sedation (e.g., propofol), and antibiotics is monitored throughout the 7-day intervention phase as well as directly before and after each intervention training.Hospital length of stay, status at hospital discharge, economic effects:To assess the economic outcomes, data from the §21 Krankenhausentgeltgesetz data will be analyzed to measure and compare length of stay, status at hospital discharge and treatment costs between study groupsHealth-related Quality of Life:Patients are given questionnaires to record their health-related quality of life (Quality of Life, SF36; WHODAS 2.0) [31]. In addition, patients are asked to indicate their current pain perception on a 100-mm VAS.

(2)Continuous examinations
Muscle Analysis II (Intramuscular, continuous measurements)By implementation of a microdialysis catheter into the M. vastus lateralis before the first basal examination is applied, it is possible to measure metabolic impact (e.g., lactate, glucose, pyruvate) and inflammatory cytokines (e.g., IL-6, IL-8, IL-10, and TNF-α) of the disease, ICU therapy, and study intervention on the muscle tissue continuously. This minimal-invasive technique enables the quantification of the acute influence of the therapy on the muscle tissue and to correlate it with changes in the other dimensions of the endpoints. The catheters are placed under sterile conditions and controlled by ultrasound after local anesthesia. In total, the catheter will stay in the muscle for 8 days. After implementation of the catheter, the flow rate at which the catheter is being flushed with the perfusion solution (NaCl) is set by a pump. During the day, the flow rate will be timed to 1 µl/min to obtain a sample of 180 µl every 3 h. Subsequent analyzation will be performed by ISCUSflex Microdialysis Analyzer (µDialysis, Stockholm, Sweden) and our cooperation partners at the Universitätsklinikum Knappschaftskrankenhaus Bochum, Ruhr-University Bochum.Systemic Immune ResponseIn addition to intramuscular measurements to analyze immune function and responses in the skeletal muscle tissue, we will evaluate the systemic immune response of the intervention. EDTA blood samples will be obtained daily during the intervention period. EDTA blood is drawn and PBMCs are isolated using Ficoll gradient centrifugation. PBMCs are then spun unto a microscope slide (Cytospin) and fixed using formaldehyde solution. Mitochondrial protein interaction for TFAM and TFB2M will be analyzed using proximity ligation assay, as previously described [6]. Briefly, cells are permeabilized and blocked using Intercept TBS Blocking buffer (Licor) and incubated with both primary antibodies overnight. After washing cells are incubated with proximity probes against mouse and goat IgG. Oligonucleotides forming the DNA circle are hybridized and ligated and subsequently amplified using a compaction oligonucleotide (PMID 26202090). PLA signals are detected with fluorescent oligonucleotides and then visualized with a fluorescent microscope.In addition, ATP content of PBMCs is analyzed using the CellTiterGlo Kit (Promega). ROS induction is measured in plasma samples, which is isolated from EDTA blood. ROS is measured using CM-H2DCFDA a fluorescent probe that changes fluorescent spectrum upon oxidation by ROS. In addition, we will measure the cytokine response in serum samples of the patient. Specifically, we will measure the cytokines IL-6, IL-8, IL-10, and TNF-α which are known for their potential role in muscle injury.

(3)In-exercise measurements
Physical and Mental Responses to Interventions:In order to analyze the impact of the interventions on patients mental and physical condition, before, each 10 min of exercise and after exercise, vital parameters such as blood pressure, pulse and oxygen saturation are measured. Furthermore, each from the beginning of the exercise intervention, each 10 min the applied medications for cardiovascular support, pain relief, and sedation are determined. For assessing the compliance of the patients to the interventions, subjective pain and exercise intensity will be obtained by visual analog scale (0–100 mm) and acute measure of recovery and stress (Akutmaß, Kurzskala, [32]).Blood Gas AnalysisBefore and after the exercise, a capillary blood sample is taken to visualize the venous blood gases (vBGA). The vBGA is used to determine carbon dioxide partial pressure (pCO_2_), oxygen partial pressure (pO_2_), oxygen content (ctO_2_), oxygen saturation (sO_2_), oxyhemoglobin fraction (FO_2_Hb), hemoglobin content (ctHb), oxygen half-saturation pressure (p50) and the concentration of lactate ([La^−^]), potassium ([K^+^]), sodium ([Na^+^]), calcium ([Ca^2+^]), bicarbonate ([HCO_3_^−^]), and chloride ([Cl^−^]).Intramuscular MonitoringDuring training interventions, the flow rate of the microdialysis catheter will be increased to 2 µl/min to get each 10 min a volume of 20 µl for analyzing the acute effects of the training interventions on muscle metabolism.

All outcome measures, there metric and timepoints are listed in Supplementary Table 2.

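### In-session vital signs and drugs are read every 10 minutes, the same period as the 5+5-minute cuff cycle, and no reading is tied to a cuff phase, so readings at exact steps sample one point of the cycle

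*Protocol article*

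**What the plan says.** Intervention description {11a} of the protocol article gives the session as "daily exercise sessions of 50 min at intervals, whereby both thighs are exercised alternately (5 min occlusion + 5 min free flow, 5 times in total"; the period is seven days. The same timetable is used in all arms. The sham procedure follows it at 20 mmHg, and electrical stimulation is coupled to the occlusion phases.

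Outcomes {12}, In-exercise measurements, sets the readings. For vital signs: "before, each 10 min of exercise and after exercise, vital parameters such as blood pressure, pulse and oxygen saturation are measured". For drugs: "each from the beginning of the exercise intervention, each 10 min the applied medications", covering cardiovascular support, pain relief and sedation. Blood gases are taken before and after the session only. During the session the microdialysis flow is raised to 2 µl/min "to get each 10 min a volume of 20 µl for analyzing the acute effects of the training interventions on muscle metabolism".

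No section says where in the cuff cycle a reading is to be taken. Safety belongs to the primary endpoints (Abstract, Methods). Adverse event reporting and harms {22} lists mild, transient circulatory changes, including in blood pressure, among the expected events.

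**The concern.** When the sampling interval equals the period of the stimulus, every sample sees the same part of the response. More sessions or more patients add readings but no new part of the cycle.

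The BFR/IPC and sham arms share a timetable and differ in cuff pressure, so a haemodynamic difference is most plausible during an occlusion or soon after a release. If the fixed reading point lies elsewhere, a change that settles within a few minutes goes unrecorded in every session, and the active arms could look like sham because of when they were read. Analysis cannot recover cuff phases that were never sampled.

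**Working it through.** **Inputs** (protocol article)
- Cycle: 5 min occlusion + 5 min free flow, 5 times; session 50 min; 7 days (Intervention description {11a}).
- Reading interval: 10 min, for vital signs and drugs (Outcomes {12}).
- Start of the series: session start for drugs; not stated for vital signs.
- Microdialysis: 2 µl/min, one fraction per 10 min (Outcomes {12}).

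**Reproducing the stated figures.** Session length: 5 × (5 + 5) = 50 min, as stated. Fraction volume: 2 µl/min × 10 min = 20 µl, as stated.

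**Cycle phase of the readings.** Phase = reading time modulo cycle length. For 10, 20, 30, 40 and 50 min, modulo 10, the phase is 0 each time. With any other start x, the times x, x + 10, x + 20 and so on all have phase x modulo 10. Either way there is one phase only. Over seven sessions that is 7 × 5 = 35 readings per patient at one phase, if the start is the same each day.

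**Where that point lies.** The text says that "both thighs are exercised alternately (5 min occlusion + 5 min free flow, 5 times in total", which allows more than one layout.
- *Layout A, one occlusion per 10-min cycle* (same thigh, or the thigh changing from cycle to cycle). Occlusions run 0–5, 10–15, 20–25, 30–35 and 40–45 min. Readings at 10 to 50 min each come 5 min after the last release, at the end of free flow. None lies within an occlusion or in the first minutes after a release.
- *Layout B, second thigh occluded while the first has free flow.* This also takes 50 min. One thigh is then occluded almost throughout, and each reading at 10 to 50 min coincides with release of the second cuff (0 min since release).
- *Five full cycles on each thigh in sequence* would take 2 × 5 × 10 = 100 min, which does not fit the 50 min.

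If the vital-sign series starts at offset x under layout A, 0 < x < 5 puts every reading in occlusion, x = 5 at release, and 5 < x < 10 every reading in free flow.

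**Other intervals, for illustration.** Starting at 0, 5-min steps cover minutes 0 and 5 of the cycle, both switch points. Steps of 4 min cover minutes 0, 2, 4, 6 and 8, so both halves are sampled. Shortening the interval alone therefore does not guarantee useful coverage.

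**Microdialysis.** Each 20 µl fraction spans 10 min, one whole cycle. At most 5 of those 10 min are occluded in the catheterised thigh, so the fraction is an average over the cycle. That differs from a reading fixed at one phase.

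**The case against.** A reader might infer that the readings miss both occlusion and cuff release. The documents do not support that in general. It follows only under layout A with readings counted from session start, and that start is written for drugs alone. Under layout B the readings coincide with a release. The vital-sign wording could also mean once within each 10-min block; the phase would then be unrecorded rather than fixed, which equally prevents a phase-matched comparison.

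A reader might also infer that the primary safety data as a whole are compromised. They are not. The safety list in Objectives {7} names drug changes, respiratory gases and daily inflammation and coagulation parameters, but not vital signs. An infusion change that persists to the next reading is seen at any phase; only one made and reversed between readings is lost. Before/after readings, blood gases, laboratory tests and the recording of observed adverse events do not depend on the 10-min grid. The planned ANCOVA on the day-7 measurement is untouched.

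Supplementary Table 2, cited for the timepoints, and the flow chart in Fig. 2 are not shown and may say more. The 10-min interval, however, is fixed in the article's own text. Patients are also under intensive care monitoring, but the article does not say that this record is captured for the trial.

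These objections narrow the point. The equality of the two periods and the absence of any link to cuff phase remain.

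**Conclusion.** The point holds in limited form. The reading interval and the cuff cycle are both 10 min, so scheduled in-session readings at exact steps sample a single point of the cycle: the end of free flow under layout A counted from session start, or the switch-over between cuffs under layout B. In either case, brief haemodynamic changes elsewhere in the cycle can be missed systematically, and these are the kind of event that the protocol expects. The resulting bias in the in-session comparison with sham is toward no difference.

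This assumes readings at exact 10-min steps and a response that settles before the next reading. The documents give no size for such a response, so the bias cannot be quantified. The point bears mainly on vital signs and only marginally on drugs. It is a worthwhile, inexpensive improvement to make before recruitment, while the trial status is still in preparation.

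**What to change.** 1. State what *alternately* means, so that the cuff state of each thigh is known at every minute of the session.
2. Schedule the in-session vital-sign readings by cuff phase: at the end of an occlusion and again shortly after a release, identically in all four arms including sham. Alternatively, take the session maximum and minimum from the bedside monitor record.
3. Describe the 10-min microdialysis fraction as a cycle average. Splitting it into two 5-min fractions of 2 × 5 = 10 µl is optional and depends on the volume that the analyser needs.

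This changes measurement timing only. With two readings per cycle, the cost is about 5 × 2 = 10 instead of 5 readings per session. If the rule of three repeats per time point (Data acquisition, under {18a}) applies in session, it is 30 instead of 15. The monitor option costs a data export instead.
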